#### Rationale for parameter selection

PC6 (Neiguan) and ST36 (Zusanli) are classic acupoints for gastrointestinal disorders. ST36 is the Lower He-Sea point of the stomach, and PC6 connects to the Yin Link Vessel. Modern studies confirm that PC6 electroacupuncture promotes gastric emptying and small intestinal transit via vagal afferent activation (38) and reduces postoperative nausea and vomiting (39). ST36 stimulation promotes distal colonic peristalsis and accelerates colonic transit through the sacral parasympathetic efferent pathway (40). Although abdominal surface stimulation may be more directly relevant to promoting bowel motility (41), it was not adopted due to potential provocation of PEG-related abdominal pain, low evidence level, and unclear optimal parameters. In contrast, limb-based PC6 and ST36 are easy to secure and do not interfere with bowel preparation. Regarding stimulation parameters (42, 43): 25 Hz is a mid-frequency dense-disperse wave that effectively activates vagal efferent fibers to promote colonic motility. A pulse width of 0.5 ms is standard for transcutaneous electrical nerve stimulation, balancing skin penetration depth and fiber selectivity. The 1-h duration overlaps the critical period of intestinal filling and enhanced peristalsis following PEG ingestion. Intensity is individualized to patient tolerance from 2 to 10 mA, ensuring efficacy without causing pain or skin injury.

#### Standardization of intervention implementation

To ensure consistency in intervention implementation across different operators, a standardized training and quality control system was established for this study. All operators uniformly completed theoretical, video-based, and manikin simulation training. They were required to achieve 100% accuracy in assessments of acupoint localization, electrode placement, and parameter settings (25 Hz, 0.5 ms, 2–10 mA) before being permitted to participate. During the study period, retraining sessions were conducted every two weeks, 10% of operational records were randomly audited, and inter-operator consistency was regularly evaluated.

### Outcomes

#### Primary outcome

The primary outcome measure was the rate of adequate bowel preparation, which was assessed by two gastroenterologists through independent review of endoscopic videos using the Boston Bowel Preparation Scale (BBPS) (33). The BBPS was applied to each of the three segments of the colon (right, including cecum and ascending colon; transverse, including hepatic and splenic flexures; and left, including descending colon, sigmoid and rectum). Each colon region received a “segment score” ranging from 0 to 3, and these scores were summed to calculate a total BBPS score (0–9) (refer to Appendix). Adequate bowel preparation was defined as a total BBPS score ≥6 with each colon segment scoring ≥2 after standard washing and air insufflation for luminal distension during colonoscopy (13, 44). Endoscopists maintained blinding to group allocation throughout the trial. All endoscopic imaging was independently evaluated by two gastroenterologists, with final diagnoses established through consensus deliberation and unresolved discrepancies resolved by a third-party senior specialist.

#### Secondary outcomes

Defecation parameters

Following TEAS/sham-TEAS interventions, patients documented their defecation parameters in the record sheets, including first defecation time, total defecation frequency, and final stool consistency.

Colonoscope outcomes

The evaluated parameters encompassed four key indicators: insertion time, withdrawal time, cecal intubation rate (CIR), and adenoma detection rate (ADR). The insertion phase was defined as commencing with initial rectal visualization and concluding when the endoscope tip traversed the ileocecal valve into the cecal caput. Withdrawal time represents the duration from cecum to anal canal during meticulous mucosal inspection in screening or diagnostic procedures without therapeutic interventions, with a minimum 6-min benchmark indicating thorough pathological evaluation. CIR, which reflects procedural completeness through comprehensive cecal visualization including anatomical landmarks, must be maintained at ≥95% to ensure examination adequacy. ADR calculated as the percentage of colonoscopies with at least one adenoma identified.

Adverse reaction

Research staff documented all adverse reactions occurring during the bowel preparation process and post-colonoscopy, including nausea, vomiting, abdominal pain, distension, headache, and dizziness (refer to Appendix). The incidence rate of adverse reactions was calculated as (number of cases with adverse reactions)/(total number of cases).

Satisfaction and follow-up colonoscopy

At the conclusion of the treatment period, all participants were surveyed regarding their satisfaction with bowel preparation and their willingness to have a follow-up colonoscopy. The details are presented in Appendix.

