Transcutaneous electrical acupoint stimulation (TEAS), a non-invasive stimulation therapy that combines the advantages of acupuncture and transcutaneous electrical nerve stimulation, has emerged as a promising therapeutic approach in clinical practice (26). As suggested by previous studies, TEAS has been shown to promote recovery of bowel function through modulation of the brain-gut axis (27–30). Recent clinical studies further demonstrate its therapeutic effects in functional gastrointestinal disorders (e.g., functional dyspepsia and chronic constipation), showing significant symptom relief and motility enhancement, potentially mediated by peripheral nerve activity regulation (30, 31). Additional study has confirmed that by enhancing parasympathetic activity, TEAS facilitates high-amplitude propagated contractions, which are critically required for efficient colonic propulsion (32). These mechanisms provide potential scientific support for TEAS in optimizing bowel preparation quality and alleviating the discomfort associated with the bowel preparation process.

To address the critical gap in evidence regarding TEAS for bowel preparation, we conducted a randomized, placebo-controlled clinical trial. This study hypothesizes that TEAS could optimize the quality of bowel preparation and alleviates bowel preparation-related symptoms, offering a potential adjunct to standard pharmacological regimens.

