### Eligibility criteria

#### Inclusion criteria

Patients eligible for the trial must comply with all of the following at randomization:

Individuals aged 18–80 years, undergoing colonoscopy for any indication, irrespective of gender;Participating in the study voluntarily and signing written informed consent.

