### Data collection and management

This study will systematically collect baseline data (demographics, medical history, abdominal symptoms assessments [using the Gastrointestinal Symptom Rating Scale (45), GSRS], intervention parameters (electrostimulation settings, acupoint localization, compliance), efficacy endpoints, and safety profiles. Data will be recorded via electronic date capture and paper-based case report forms (CRFs) during screening, intervention, and follow-up phases, with real-time entry and logic verification. Two individuals will independently enter and verify the data for error correction, and participant information will be anonymized. The Ethics Committee will conduct random audits for quality control to ensure the authenticity and traceability of the data.

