### Statistical analysis

All statistical analyses were performed using SPSS 29.0 and GraphPad Prism 10.4, adhering to the intention-to-treat (ITT) principle. Continuous variables were tested for normality using the Shapiro–Wilk test; normally distributed data were expressed as mean ± standard deviation, and non-normally distributed data as median [interquartile range]. Categorical variables were presented as frequencies and percentages. For the primary outcome (rate of adequate bowel preparation), a multivariable logistic regression model was employed to adjust for baseline covariates. Missing data were handled using Multiple Imputation by Chained Equations (MICE); 20 imputed datasets were generated, and the imputation model included all baseline variables, the grouping variable, and the primary outcome measure. To control the type I error rate for multiple secondary outcomes, a hierarchical strategy was adopted. The primary outcome was tested at *α* = 0.05. Among secondary outcomes, colonoscopy indicators were designated as key secondary endpoints and were corrected using the Holm-Bonferroni method. For these endpoints, insertion and withdrawal times (continuous variables) were compared using independent *t*-tests or Mann–Whitney *U* tests as appropriate, and cecal intubation and adenoma detection rates (categorical variables) were compared using Chi-square or Fisher’s exact tests. The remaining secondary outcomes, including bowel movement parameters, patient satisfaction scores, and adverse reactions, were treated as exploratory analyses; no multiplicity correction was applied, and *p*-values are presented for descriptive reference only. Safety profiles were described by comparing the incidence and severity of adverse events (Chi-square test) and patient satisfaction (Wilcoxon rank-sum test). Protocol deviations were addressed by per-protocol sensitivity analyses to verify the robustness of the results. A two-sided *p* < 0.05 was considered statistically significant.

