### Adverse reaction

Adverse reaction associated with bowel preparation and colonoscopy procedures—including nausea, vomiting, abdominal pain, bloating, headache, and dizziness—were prospectively categorized by blinded independent assessors.

1) Transient symptoms requiring no intervention, with preserved procedure tolerability;
2) Symptom-driven procedural pauses (<5 min) without compromising examination completion;
3) Intolerable symptoms necessitating premature procedure termination;

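### Adverse reactions, the most direct measure of the symptom-relief hypothesis, are compared without adjustment although baseline GSRS is already collected

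*Protocol article*

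**What the plan says.** All references are to the protocol article.

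- **Hypothesis.** The Introduction expects that "TEAS could optimize the quality of bowel preparation and alleviates bowel preparation-related symptoms". The end of the Discussion repeats the second aim, naming bloating and nausea.
- **Outcome.** Secondary outcomes, under Adverse reaction: "Research staff documented all adverse reactions occurring during the bowel preparation process and post-colonoscopy, including nausea, vomiting, abdominal pain, distension, headache, and dizziness". The summary measure is a simple proportion: "The incidence rate of adverse reactions was calculated as (number of cases with adverse reactions)/(total number of cases"). The Appendix describes the events as "Adverse reaction associated with bowel preparation and colonoscopy procedures" and has blinded assessors sort them into three grades by tolerability and disruption of the procedure.
- **Analysis.** Statistical analysis: "Safety profiles were described by comparing the incidence and severity of adverse events (Chi-square test"). Adjustment for baseline covariates is stated for the primary outcome only. Adverse reactions are among the outcomes that "were treated as exploratory analyses; no multiplicity correction was applied, and *p*-values are presented for descriptive reference only".
- **Baseline data.** Data collection and management lists "abdominal symptoms assessments [using the Gastrointestinal Symptom Rating Scale (45), GSRS") among the baseline items. No section links it to the adverse-reaction comparison.
- **Population.** Inclusion criteria admit people "undergoing colonoscopy for any indication, irrespective of gender"; the Recruitment section restricts the cohort to inpatients.

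**The concern.** Nausea, abdominal pain and distension are on the adverse-reaction list, and they are also symptoms that may bring an inpatient to colonoscopy. A patient who enters with such a symptom is more likely to have it recorded during preparation, whichever arm he or she is in. Variation of this kind has nothing to do with PEG or TEAS, yet a crude two-by-two comparison leaves it all in the contrast.

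The plan already holds a baseline measurement aimed at these abdominal symptoms and does not use it in the comparison where it is most likely to help. At stake is sensitivity: a real reduction in preparation-related symptoms could look smaller than it is, or be reported as absent.

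**Working it through.** **1. The plan's own figure.** The article gives no expected rate, effect or power for adverse reactions, so there is no stated figure to reproduce for this outcome. Its one calculation, for the primary outcome, does reproduce. With 70% v 85%, two-sided 5%, 90% power and pooled variance under the null, n = 161 per group; 161/0.80 = 201.25, rounded up to 202 per group and 404 in total. This point does not touch it.

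**2. Inputs for an illustration.**

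- n = 202 per arm and two-sided 5%: from Sample size.
- Preparation-related symptoms under sham, p_S = 37%: borrowed from the intolerance rate of a cited trial in the Discussion. That rate includes anal irritation, which is not on this trial's list, so it is only a stand-in.
- The same rate under TEAS, p_T = 25%: assumed.
- Share k of patients whose pre-existing symptom persists and is recorded as a reaction in either arm: not in the article, varied from 0 to 35%.

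**3. Formulas.** Crude rate in an arm = k + (1 − k)p. Crude difference = (1 − k)(p_S − p_T), so the difference shrinks by the factor (1 − k). Power = Φ{[d√n − 1.96√(2p̄(1 − p̄))] / √[p₁(1 − p₁) + p₂(1 − p₂)]}, where d is the difference and p̄ the mean of the two rates.

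**4. Crude comparison.**

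| k | Sham | TEAS | Difference (points) | Power |
|---|---|---|---|---|
| 0 | 37.0% | 25.0% | 12.0 | 74% |
| 15% | 46.5% | 36.3% | 10.2 | 55% |
| 25% | 52.8% | 43.8% | 9.0 | 44% |
| 35% | 59.1% | 51.3% | 7.8 | 35% |

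For k = 25%: d√n = 0.09 × √202 = 1.279; the null term is 1.385; the denominator is 0.704; (1.279 − 1.385)/0.704 = −0.15, and Φ(−0.15) = 0.44.

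**5. What adjustment could recover at k = 25%.** In this simple model the patients with persisting symptoms are cases in both arms and carry no information on treatment. A covariate that identified them perfectly would leave the comparison in the rest: 202 × 0.75 ≈ 151 per arm, 37% v 25%. Then 0.12 × √151 = 1.475; (1.475 − 1.282)/0.649 = 0.30; Φ(0.30) = 0.62. Baseline GSRS will not identify them perfectly, so the gain from adjustment lies somewhere between 44% and about 62%.

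**6. A different assumed effect.** With a risk ratio of 0.70 (37.0% v 25.9%), crude power is 67% at k = 0, 54% at 10%, 43% at 20% and 35% at 30%. With a risk ratio of 0.60 it is 91%, 80%, 67% and 55%. The pattern is the same, but the level depends heavily on the assumed effect.

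**The case against.** **The text may already exclude prior symptoms.** A reader might infer that pre-existing symptoms count as adverse reactions and that the symptom comparison is therefore diluted. The article does not support this. It speaks of reactions that occur in a window, and the Appendix ties them to the preparation and the procedure, with blinded assessors sorting them. On that wording, longstanding bloating unrelated to PEG need not be a reaction at all. The absence of an explicit new-or-worse rule is a detail that an article may leave to the full protocol, so it is no fault here. This part of the objection stands. It does not remove the point about the analysis: imperfect attribution would let some prior symptoms through, and the test named in the article cannot allow for them.

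**The outcome is exploratory.** This also stands. The p-values are descriptive, so power at the 5% level serves only as a yardstick for precision. Severity and satisfaction are compared too, and the satisfaction scale is anchored on adverse effects. Incidence is thus the most direct measure of symptom relief, not the only one.

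**Randomisation protects the comparison.** True. Any carry-over falls on both arms alike, and the categorisation is blinded. Neither arm is favoured.

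**The inputs are invented.** Neither k nor the TEAS effect is in the article. The Exclusion criteria remove cancer, other serious organic disease, most previous digestive surgery and recent motility-affecting drugs, so a high k should not be presumed.

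**Redefining the outcome gains less than it seems.** Counting only new or worsened symptoms at k = 25% gives 0.75 × 37% = 27.8% v 0.75 × 25% = 18.8%: the same 9.0 points as the crude count, with power of about 57%. It would also require GSRS ratings to be compared with a different grading scale. That is a reason to prefer covariate adjustment to a filtered event count.

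**Conclusion.** The point holds as a missed gain in precision. The article fixes an unadjusted chi-square for the most direct measure of half of its hypothesis, while collecting a baseline measure of overlapping abdominal symptoms that the comparison does not use. The consequence is confined to lost sensitivity in an exploratory outcome. The primary result, the sample size and the validity of the comparison between arms are unaffected.

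The size is undetermined. It depends on the share of patients whose prior symptoms persist and are recorded, and on how well baseline GSRS predicts the outcome; the article gives neither. Under the assumed 37% v 25% with a 25% share, power is about 44% crude, with about 62% an optimistic bound after adjustment. If assessors exclude prior symptoms reliably, the share is near zero and the loss from this source is small.

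**What to change.** In Statistical analysis, compare adverse-reaction incidence between arms with a logistic regression that includes the baseline GSRS score, at least for the abdominal symptoms. Keep the crude incidence by arm and the chi-square test as the safety description, so that no safety information is lost. Specify the model before unblinding. The adjusted odds ratio is conditional on baseline and not on the same scale as the crude difference, so report the two side by side and label them.

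The cost is a sentence or two of wording and one further model; the baseline data are already planned. The limits are that the article presents the GSRS as an abdominal-symptom measure, so it offers nothing for headache or dizziness, and that the gain will be small if GSRS predicts the recorded reactions poorly.

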### Sample size

The sample size was calculated using a two-sample proportion test, with the following parameters: a two-sided significance level (*α*) of 0.05, a statistical power of 90% (*β* = 0.1), an expected qualified preparation rate of 70% for the sham TEAS group, and 85% for the active TEAS group. The calculated minimum evaluable sample size was 161 per group. Accounting for a 20% dropout rate, a total of 404 subjects were planned, with 202 subjects allocated to each group.

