Acupuncture is a nonpharmaceutical technique that originated in China and has been used for over 3,000 years. TEAS is a modification of traditional acupuncture (58–60), which combines the advantages of acupuncture and percutaneous electrical nerve stimulation. Unlike traditional acupuncture requiring skin penetration, this transcutaneous approach exhibits notable application prospects via its non-invasive nature, user-friendly operation, and portability (27, 61–63), while concurrently reducing infection risks and improving patient compliance (64). In recent years, a growing number of investigations have put a spotlight on the therapeutic effects of TEAS in intestinal dysmotility disorders. Clinical trials demonstrated that ST36 acupoint stimulation effectively enhances spontaneous bowel movements, alleviates constipation symptoms, and improves quality of life (65), while PC6 application demonstrates marked efficacy in reducing postoperative nausea and vomiting incidence within 24 h (66). While transabdominal or abdominal surface stimulation is theoretically more direct, limb acupoint TEAS is a superior adjunctive choice based on current evidence and operational feasibility. This study implemented a standardized stimulation parameter protocol (0.5-ms pulse width, 25 Hz frequency, and 2–10 mA amplitude) (42, 43, 67), developed based on prior clinical trial evidence to ensure intervention stability and experimental reproducibility. This study recruited only inpatients, which may limit the generalizability of our findings to the broader outpatient colonoscopy population. The inpatient setting was chosen to ensure protocol adherence and intervention fidelity, but future multicenter, pragmatic trials in outpatient settings are needed to validate the real-world applicability of TEAS as an adjunct to bowel preparation. Additionally, although we standardized endoscopist experience and withdrawal time, ADR remains influenced by multiple operator-dependent factors, and residual confounding cannot be fully excluded.

This protocol employs validated stimulation parameters (25 Hz frequency, 60-min sessions) combined with standardized laxative regimens, aiming to establish TEAS as a safe strategy for enhacing bowel preparation and alleviating adverse effects (e.g., bloating and nausea).

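### The only adverse-reaction rate the plan defines pools all symptoms, so a benefit confined to nausea or bloating, the symptoms its aim centres on, can be diluted (minor)

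*Protocol article*

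**What the plan says.** **Definition.** The Adverse reaction part of Secondary outcomes has staff record reactions during preparation and after colonoscopy. It names nausea, vomiting, abdominal pain, distension, headache and dizziness as included. It then gives one formula: "The incidence rate of adverse reactions was calculated as (number of cases with adverse reactions)/(total number of cases"). That is the share of patients with any reaction.

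**Analysis.** The Statistical analysis section describes safety by "comparing the incidence and severity of adverse events (Chi-square test"). It places adverse reactions among the exploratory outcomes, without multiplicity correction and with p-values for description only. The Appendix grades each reaction by its effect on the procedure, not by type of symptom. No symptom-specific comparison is stated.

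**Aim.** The Introduction ends with a two-part hypothesis: better preparation quality, and relief of symptoms related to preparation. The rationale for parameter selection and the Discussion both credit PC6 with reducing nausea and vomiting. The Discussion closes on "alleviating adverse effects (e.g., bloating and nausea"). No section says how TEAS would act on headache or dizziness.

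**The concern.** The formula and the aim do not match. The aim points to a few gastrointestinal symptoms, whereas the formula counts a patient once for any reaction of any kind. A patient spared nausea but dizzy afterwards counts the same as a patient with both.

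Two things follow:

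- The defined rate cannot answer whether nausea or bloating fell.
- If TEAS helps only one symptom, the difference in the pooled rate is smaller than the difference in that symptom and is measured against a larger background. A real benefit could be reported as no clear difference in adverse reactions.

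There is also a reporting risk. If symptom-level results are chosen only after the data are seen, whichever symptom happened to fall can be put forward as the finding.

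**Working it through.** **The plan's own figure.** The Sample size section assumes "an expected qualified preparation rate of 70% for the sham TEAS group, and 85% for the active TEAS group", with two-sided α = 0.05 and 90% power. The pooled-variance formula without continuity correction gives

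n = [1.96·√(2·0.775·0.225) + 1.2816·√(0.70·0.30 + 0.85·0.15)]² / 0.15² = 160.8, so 161 per group.

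This agrees with the text: "The calculated minimum evaluable sample size was 161 per group". Allowing for 20% dropout, 161/0.8 = 201.25, so 202 per group and 404 in total. The primary sample size is sound and is not affected here. It supplies the two group sizes used below.

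**Inputs for the illustration.**

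- n = 202 (randomised) or 161 (evaluable) per arm, from Sample size.
- Any-reaction rate under sham of 37%. *Assumption*, borrowed from the gastrointestinal intolerance rate of a cited trial in the Discussion. That trial's symptom list differs in part: it names anal irritation and does not name headache or dizziness.
- Nausea rate under sham of 15%, halved by TEAS to 7.5%. *Assumption*; the range 10% to 25% is shown below.
- Symptoms occur independently, and TEAS changes nausea only. *Assumption*.

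**Pooled rate under TEAS.** Let b be the chance of any reaction other than nausea. Then 1 − 0.37 = (1 − b)(1 − 0.15), so b = 1 − 0.63/0.85 = 25.9%. Under TEAS the any-reaction rate is 1 − (0.63/0.85)·0.925 = 31.4%. A fall of 7.5 points in nausea therefore appears as a fall of 5.6 points in the pooled rate.

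**Power** (two-sided 0.05), with d the difference and p̄ the mean of the two rates:

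Φ{ [d√n − 1.96·√(2p̄(1−p̄))] / √(p₁(1−p₁) + p₂(1−p₂)) }

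- Nausea alone, n = 202: (1.066 − 0.876)/0.4437 = 0.428, power 67%.
- Pooled rate, n = 202: (0.790 − 1.315)/0.6698 = −0.784, power 22%.
- Nausea alone, n = 161: (0.952 − 0.876)/0.4437 = 0.171, power 57%.
- Pooled rate, n = 161: (0.705 − 1.315)/0.6698 = −0.910, power 18%.

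**Range**, with one symptom halved and the sham any-reaction rate held at 37%:

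| Sham rate of the symptom | Pooled rate under TEAS | Power at 202: alone / pooled | Power at 161: alone / pooled |
|---|---|---|---|
| 10% | 33.5% | 48% / 11% | 40% / 10% |
| 15% | 31.4% | 67% / 22% | 57% / 18% |
| 20% | 29.1% | 81% / 39% | 71% / 32% |
| 25% | 26.5% | 90% / 62% | 82% / 53% |

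**Benefit spread over two symptoms.** If nausea and bloating are both halved from 10% each, the pooled rate falls to 29.8% and pooled power at 202 is 33%, against 48% for either symptom alone. If both are halved from 15% each, the pooled rate falls to 25.4% and pooled power is 71%, against 67% for either alone. Dilution is thus marked when one symptom responds, and can vanish when several do.

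**The case against.** **The aim is wider than two symptoms.** The hypothesis speaks of preparation symptoms in general, bloating and nausea are given only as examples, and the reaction list is open-ended. An overall rate does answer a general question about burden. This stands, and it is why the any-reaction rate should be kept as a summary. It does not show that the rate answers the specific expectation attached to PC6.

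**Symptom-level tables are not ruled out.** Reactions are recorded by name, categorical data are to be shown as frequencies and percentages, and an adverse-event table may sit in the full protocol or SAP, neither of which is shown. This also stands in part. The point is not that a table is missing. It is that the one rate the article does define fits the stated aim poorly.

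**The tier is exploratory.** No confirmatory claim depends on this comparison. This stands and limits the severity. The same status means that separate reporting carries no multiplicity penalty.

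**Two stronger readings are tempting and are not supported.**

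- A reader might infer that the plan expects stimulation to increase abdominal pain, which would cancel a fall in nausea inside the pooled rate. The words "potential provocation of PEG-related abdominal pain" concern abdominal surface stimulation, which was not adopted. The limb points actually used are said not to interfere with preparation. Cancellation is arithmetically possible: with an assumed 8% pain rate, a halved 15% nausea rate would be offset if pain rose to 1 − 0.92·0.85/0.925 = 15.5%. Nothing in the plan predicts such a rise.
- A reader might infer that splitting the symptoms always gains power. It does not. Suppose nausea or vomiting and distension are equal, independent components that jointly fall from 25% to 15%, over an unaffected 15% background. Each component goes from 13.4% to 7.8%, with about 45% power at 202 per arm. The pooled rate goes from 36.3% to 27.8%, also with about 45%.

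**Conclusion.** The point holds as a minor one. The article defines a single any-reaction rate, while its symptom aim centres on nausea, vomiting and bloating. As defined, that rate cannot show whether those symptoms fell, whatever the power.

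The loss of power is real when the benefit lies in one symptom. In the central illustration it is 67% against 22% at 202 per arm, and 57% against 18% at 161. These figures rest on assumed symptom rates, independence and a borrowed 37% anchor, so they show the order of size and do not forecast this trial. They do not carry over to a benefit spread evenly over several symptoms. The primary outcome and the sample size are untouched.

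**What to change.** In Secondary outcomes (Adverse reaction) and in Statistical analysis:

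1. Name two exploratory symptom comparisons in advance: (a) nausea or vomiting, and (b) distension or bloating. Give each as a risk difference between arms with a 95% CI.
2. Report abdominal pain, headache, dizziness and any other recorded reaction individually, as descriptive output.
3. Keep the any-reaction rate as an overall summary.

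The data are already collected by symptom, so the cost is a change of wording and a few extra table rows. The downside is a few more exploratory comparisons, in a tier where p-values are already descriptive only.
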